### Randomisation

Randomisation will be carried out after consent to participate in the trial has been given and the baseline assessment has been completed. Participants will be randomised through an independent web-based service provided by the UKCRC-registered King’s Clinical Trials Unit (Reg. No. 053). The randomisation procedure will employ random permuted blocks of random size, which will maintain pre-randomisation allocation concealment. We will stratify the randomisation lists by a Severe Mental Illness (i.e. psychotic illness)/Other Mental Illness factor, since this is an important prognostic factor. We will also stratify by borough for logistical reasons, so that treatment cases are equitably allocated across therapists.

### Blinding procedure

We will not be able to blind participants to treatment group. Similarly, the therapists cannot be blind to allocation as they will deliver the intervention. However, the research workers completing outcome assessments will be blinded to treatment allocation. Should they be accidentally unblinded during the assessment, we will record which outcomes were completed blind and allocate a new assessor for any subsequent assessments. Post-randomisation assessors will work separately from the research and clinical teams to minimise the likelihood of unblinding. We will ask research workers to guess the allocation group for each participant at each assessment as a test of the success of our efforts to maintain blindness. We will report any instances of unblinding in subsequent publications. The end of the trial will be defined as the last follow-up assessment at 24 weeks. Routine-care participants may continue to receive therapy beyond this point, and we will continue to collect sessional measures, but this will be to inform therapy development, implementation and training, rather than as part of the outcomes of the study. Analyses will be completed blind to allocation.

### Trial monitoring and oversight

We have established an Independent Trial Steering Committee (ITSC), comprising an independent experienced trialist as chair, a CAMHS researcher and clinician who are not involved in the trial, the trial statistician and two independent CAMHS carers or service users. Sponsor and funder representatives will be invited as required. We planned for the ITSC to convene annually at 6, 18 and 30 months; meetings have taken place at 9, 15, 21 and 27 months, with a final meeting planned for 35 months. The ITSC will oversee the progress of the trial and will review any proposed protocol changes. Any changes agreed by the ITSC will then be put to all relevant regulatory bodies including the REC, the sponsors and the funder. Approved changes will be updated in the protocol and trial registry.

### Data monitoring

Based on pilot studies, we do not anticipate risks to participant safety as a direct result of the study and will not, therefore, be conducting any interim data analysis and will not convene a separate Data Monitoring Committee. The trial may be prematurely discontinued by the sponsor, the chief investigator or the REC on the basis of new safety information or for other reasons given by the Ethics Committee or Trial Steering Committee.

If the trial is prematurely discontinued, active participants will be informed and no further participant data will be collected. Arrangements will be made directly with the local clinical service to ensure that the safety and wellbeing of the young people and their families is not compromised by this process.

### Data management

We will use paper assessment packs and enter data into electronic databases. Patient data will be pseudonymised for the duration of the study and fully anonymised after the retention period specified in institutional policies (currently, 12 years) has passed. Fully identifiable personal details will be kept on paper in a locked filing cabinet in a locked or occupied office; on secure NHS computers; and, encrypted, on password-protected computers in the university. Pseudonymised data will be stored on personal laptop computers, using recommended secure encryption methods. All trial data will be stored in line with the Data Protection Act [93].

Separate databases will be used for: (1) baseline demographics, (2) repeated clinical measures (separate database for each time point), (3) child and parent measures, (4) allocation, (5) sessional therapy measures, (6) feedback measures and (7) therapy delivery and adherence. The allocation database will be accessible only to the lead research worker (who will not conduct post-baseline assessments) and the trial statistician until the study is completed. Outcome assessments will be carried out by researchers who do not have access to therapy or feedback data. Data will be checked and cleaned against original paper copies and a final database returned to the statistician, who will combine with allocation data for analysis.

### Safety monitoring and adverse event reporting

We will monitor adverse events for all participants by logging any reported by the participant or their network, or the clinical or research team. We will also check the medical record for unreported adverse events at each time point (for the previous 6 months at baseline; since the last assessment at 16 and 24 weeks). Events will be rated for seriousness according to the impact on the participant’s day-to-day life. The event will be considered to be related to the trial if, in the view of the participant, a member of their network, the clinical team or the research team, it is reported to be related. The primary concern in any report will be to work with the clinical team and other emergency services as appropriate to ensure the participant’s safety. Serious adverse events that are related to the trial will be discussed with the ITSC and reported to the trial sponsor and the REC within 15 days.

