**Methods:**

The CUES+ study is a randomised controlled trial comparing CBT-UED plus routine care to routine care alone. CBT-UED comprises up to 16 sessions, including up to 12 individual and up to four family support meetings, each lasting around 45–60 min, delivered weekly. The primary outcome is emotional distress. Secondary outcomes are change in UEDs, risk events (self-harm, attendance at emergency services, other adverse events) and health economic outcomes. Participants will be randomised in a 1:1 ratio after baseline assessment. Randomisation will be stratified by borough and by severity of mental health presentation: ‘severe’ (an identified psychotic or bipolar disorder) or any ‘other’ condition. Outcomes will be assessed by a trained assessor blind to treatment condition at 0, 16 and 24 weeks. Recruitment began in February, 2015 and is ongoing until the end of March, 2017.

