#### Intervention

The therapy will comprise up to 16 sessions, delivered over 16 weeks, including up to 12 sessions of individual CBT, adapted for adolescents, and up to four family support sessions. The intervention will be delivered in addition to routine care (specialist care coordination, practical and emotional support for the young person and their family, and medication as appropriate), and will be compared to routine care alone. After the 24-week assessment, adolescents in the routine care condition will be offered the intervention.

Intervention will not ordinarily exceed a total of 16 sessions (notwithstanding requirements to extend therapy to ensure safety and wellbeing), but may exceed 16 weeks of delivery, as needed to accommodate, for example, holidays and examination periods. The intervention content has been developed from our earlier inpatient protocols for individual and family work with young people with psychosis [32], and adapted for young people with UEDs in the general population [33] and in services for children with emotional and behavioural problems [34]. Pilot work has demonstrated feasibility, acceptability and potential helpfulness of the intervention [32, 33]. Individual work focusses on developing a collaborative understanding of UEDs, together with skills in affect regulation, managing negative automatic thoughts, behavioural tests, dealing with social difficulties and adverse life events, recognising and compensating for cognitive biases, and a section on taking the work forward and preventing future difficulties. Where there has been trauma, therapists complete pre- and post-therapy measures of event appraisals and post-traumatic cognitions to aid therapy [44]. Therapy is tailored to take account of the developmental stage and presenting issues of the child/young person, with an emphasis on identity formation, understanding of the self in relation to the experience of psychosis/UEDs, social inclusion and self-esteem. Therapy materials are designed to be fun, interactive and engaging. Family support is crucial when working with young people, and has been requested by parents consulting on our studies. Family work comprises recognition and understanding of the child’s difficulties, sharing the intervention plan, and troubleshooting any key familial difficulties.

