### Measures

#### Outcomes and timeline

Following informed consent from each participant, all outcomes will be assessed by a trained study researcher. Demographic/clinical characteristics (age, gender, ethnicity, parent-reported developmental delays, family circumstances, diagnoses), brief cognitive functioning (word reading, working memory and general intelligence) and history of adverse life events and bullying will be assessed at baseline [45–50]. Outcomes will be assessed at baseline (0 weeks) then at 16 weeks and 24 weeks post randomisation, irrespective of treatment duration. Assessments will not be completed more than 2 weeks after the planned assessment time point. Outcomes and all measures are listed in Table 1 and will be completed according to the schedule in Fig. 2.

**Table 1 Tab1:** Coping with Unusual ExperienceS for 12–18 year olds (CUES+): list of measures

Measure	Completed	
	By	At
Primary outcome		
1. Strengths and Difficulties Questionnaire-Emotional Problems (SDQ-E) [41, 42]	1	0,1
Main secondary outcomes		
2. Unusual Experiences Questionnaire – severity score (UEQ) [10, 14, 39]	1	0,1
3. Self-harm (Development and Wellbeing Scales, DAWBA) [45]	1	0,1
4. Child Clinical Service Receipt Inventory (CSRI) [51]	2,3	− 1,2
5. EuroQol Health Questionnaire, youth (EQ5D-Y) [52–54]	1,2	0,2
Other secondary child outcomes		
6. Strengths and Difficulties Questionnaire (SDQ) [41, 42]	1,2	0,1,2
7. Unusual Experiences Questionnaire (UEQ) [10, 14, 39]	1,2	0,1,2
8. Child Global Assessment Scale (C-GAS) [86]	3	0,1,2
9. Health of the Nation Outcome Scales for Children and Adolescents (HoNOSCA) [87, 88]	3	0,1,2
10. Revised Child Anxiety and Depression Scales (RCADS) [55]	1,2	0,1,2
11. Elevated Mood Scales [56–58]	1,2	0,1,2
12. Me and My School, behavioural problems (M&MS) [59]	1,2	0,1,2
13. Difficulties in Emotion Regulation Scale (DERS) [60]	1	0,1,2
14. Adolescent Dissociative Experiences Scale (A-DES) [61]	1	0,1,2
15. Child Revised Impact of Events Scale (CRIES-13) [62]	1	0,1,2
16. Eating disorder screen (DAWBA) [45]	1	0,1,2
17. Maudsley Addictions Profile (MAP) [63]	1	0,1,2
18. Time budget of activities and peer relationships [64–66]	1	0,1,2
19. Beliefs about problems (BAP) [69–72]	1	0,1,2
20. Brief Core Schema Scale [27, 68]	1	0,1,2
21. Jumping to conclusions [26, 73]	1	0,1,2
Secondary parent outcomes		
22. Five Minute Speech Sample (FMSS) [74]	2	0,1
23. Brief Illness Perception Questionnaire (BIPQ) [36, 69]	2	0,1

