#### Secondary outcomes

Secondary outcomes will be child-reported UED severity at 16 weeks, assessed using the self-report UEQ [10, 14, 39]. Self-reported self-harm [45] and adverse events including attendance at accident and emergency services, and economic costs, including quality-adjusted life years (QALYs) [51–54] will also be assessed.

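### Adverse events are logged from any reporter, but only the CBT-UED arm has up to 16 extra therapist contacts, so recorded 'other adverse events' may be inflated in that arm

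*Protocol article*

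**What the plan says.** **Status of the outcome.** The abstract's Methods paragraph lists among the secondary outcomes "risk events (self-harm, attendance at emergency services, other adverse events". The Secondary outcomes section again includes "adverse events including attendance at accident and emergency services". In Table 1 the block of main secondary outcomes contains "3. Self-harm (Development and Wellbeing Scales, DAWBA) [45", the UEQ severity score, the CSRI and the EQ-5D-Y. The logged adverse events have no row in the table. Under Statistical analysis, secondary outcomes other than economic ones are analysed in the same way as the primary outcome, that is, as a comparison between arms.

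**How events are found.** Safety monitoring and adverse event reporting gives two routes. The first is open reporting, "logging any reported by the participant or their network, or the clinical or research team". The second follows at once: "We will also check the medical record for unreported adverse events at each time point", over the same windows for every participant.

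**Contact by arm.** Under Intervention, "The therapy will comprise up to 16 sessions, delivered over 16 weeks", in addition to routine care. Routine-care participants are offered the therapy only after the 24-week assessment. Therapists are CAMHS clinicians who are not blind to allocation (Therapists; Blinding procedure), and while the trial runs they do not coordinate care for participants allocated to routine care.

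**Oversight.** "Serious adverse events that are related to the trial will be discussed with the ITSC" and go to the sponsor and the ethics committee. The plan "will not convene a separate Data Monitoring Committee" and has no interim analysis.

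**The concern.** A fair comparison of event counts needs the same chance of recording an event in each arm. Here one reporting route is open-ended, and one arm has up to 16 more occasions on which a young person or parent may tell a clinician about an event. The therapists who hear it are trained and supervised by the trial. The article does not say that events learned only in this way are marked or kept apart.

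Two readings would be at risk. An apparent excess under CBT-UED could not be told apart from closer observation. A true reduction could be cancelled by better detection. Both matter in services whose usual entry criterion, according to Participants and setting, is risk of harm to self or others.

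A smaller, related issue is that the only serious events the article commits to the steering committee are those also reported as related to the trial. A routine-care participant has received no trial therapy to which an event could be attributed, so this filter may also work differently by arm.

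**Working it through.** The article states no event rate, detection rate or figure for record completeness, so there is no figure to reproduce. What follows is an illustration with equal true rates in the two arms. The only input taken from the document is 60 participants per group (Sample size).

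**1. Which sources differ by arm**

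| Source | CBT-UED | Routine care |
|---|---|---|
| Medical record check at 16 and 24 weeks | yes | yes |
| Self-harm on the DAWBA, child-reported, blind assessor, 16 weeks | yes | yes |
| CSRI service use, 6 months after baseline | yes | yes |
| Reports from participant, network, routine clinical team | yes | yes |
| Up to 16 therapy sessions before 24 weeks | yes | no |

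Only the last row differs.

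**2. Ratio of recorded events, all common sources pooled.** Let c be the share of events captured by the sources that both arms have, and f the share of the remainder that therapy contact finds. Both are assumptions.

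Recorded ratio = [c + f(1 − c)] / c

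| c | f = 0.5 | Ratio |
|---|---|---|
| 0.50 | 0.750 / 0.50 | 1.50 |
| 0.60 | 0.800 / 0.60 | 1.33 |
| 0.80 | 0.900 / 0.80 | 1.13 |
| 0.90 | 0.950 / 0.90 | 1.06 |
| 0.95 | 0.975 / 0.95 | 1.03 |

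If therapists find only a fifth of the remainder (f = 0.2), then c = 0.80 gives 0.84 / 0.80 = 1.05.

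**3. What the record check does.** Suppose open reporting finds 50% of events in routine care and 80% under CBT-UED, and the record captures a share r in both arms, independently. Detection = 1 − (1 − reported)(1 − r).

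| r | Routine care | CBT-UED | Ratio |
|---|---|---|---|
| 0 | 0.50 | 0.80 | 1.60 |
| 0.3 | 0.65 | 0.86 | 1.32 |
| 0.5 | 0.75 | 0.90 | 1.20 |
| 0.7 | 0.85 | 0.94 | 1.11 |
| 0.9 | 0.95 | 0.98 | 1.03 |
| 1.0 | 1.00 | 1.00 | 1.00 |

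The check shrinks the imbalance steadily, and removes it only if the record is complete.

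**4. Effect on a comparison of 60 v 60.** Assume that 30% of participants in each arm truly have an event. The last column is the chance of a significant excess under CBT-UED at the two-sided 0.05 level. The nominal value in that direction is 2.5%.

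| Detection, routine care v CBT-UED | Recorded | Extra participants (60 × difference) | Chance |
|---|---|---|---|
| 0.60 v 0.90 | 18% v 27% | 5.4 | about 22% |
| 0.80 v 0.90 | 24% v 27% | 1.8 | about 6% |
| 0.90 v 0.95 | 27% v 28.5% | 0.9 | about 4% |

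Depending on inputs that the article does not give, the distortion may be material or negligible.

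**The case against.** The case on the other side is substantial.

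- **The record check is systematic and identical in both arms**, and step 3 shows that a good record leaves little bias. This stands, with one reservation. The therapists are CAMHS clinicians, so what they hear in sessions may be written into the very record that is checked, while an event never disclosed in routine care appears nowhere.
- **Routine care is not an absence of contact.** Both arms have care coordination and practical and emotional support, so the clinical team in the logging rule serves both. This stands, but CBT-UED is given on top of it.
- **The named risk events largely have sources common to both arms.** Self-harm is child-reported at 0 and 16 weeks, and the 16-week assessor is blind. Emergency attendance leaves a record, and service use is collected through the CSRI. This stands. The participants know their allocation, but the DAWBA gives each arm the same opportunity to report. The problem therefore falls mainly on other adverse events. A reader might infer that the whole risk-event outcome is biased, and the article does not support that.
- **A source field is a detail that an article may leave to the full protocol or event log.** This is fair for the field itself. The point here is that the logging rule as stated, combined with the stated between-arm analysis, gives unequal ascertainment.
- **On oversight**, relatedness has a low threshold, since the view of any one party is enough. The article gives a reason for having no separate monitoring committee, and the trial can be stopped on new safety information. A reader might infer that unrelated serious events are withheld from the steering committee. The text does not say so; it only makes no commitment to show them.

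**Conclusion.** The point holds in a limited form. Adverse events are a secondary outcome that is to be compared between arms, the logging rule accepts any reporter, and only one arm has the additional contacts. Unequal contact may therefore inflate recorded other adverse events under CBT-UED or mask a true reduction, and the safeguards present in both arms reduce this only in part.

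Two stronger readings are not supported. One is that the CBT-UED count will be inflated: at 90% capture by common sources the ratio is already down to about 1.06, and the article gives no capture rate. The other is that a main secondary outcome is compromised: Table 1 does not list the logged adverse events under that heading.

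The range of about 1.50 to 1.03 rests wholly on assumed common capture of 50% to 95% and on therapists finding half of the rest. It shows what is possible and does not estimate the bias. The primary outcome is not touched. The change is still worth making because it costs little and removes an ambiguity that the results could not otherwise resolve.

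**What to change.** 1. Tag each logged event with its source or sources. For events already logged, assign the source where the log shows it.
2. Base the between-arm comparison on sources that run alike in both arms: DAWBA self-harm at 16 weeks with a blind assessor, CSRI service use to 24 weeks, and emergency or hospital attendances from the record check. Limiting the record to attendances avoids bringing session disclosures back in through clinical notes. The DAWBA should not be relied on at 24 weeks, since Table 1 schedules it at 0 and 16 weeks only.
3. List separately, for the CBT-UED arm, events known only through therapy sessions, so that no safety information is lost.
4. Secondary point: give the independent members of the steering committee a table of all serious events by arm, regardless of relatedness. According to Trial monitoring and oversight, only the 35-month meeting remains, and Status reports 111 of 120 participants randomised, so this now serves final review more than protection during recruitment.

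The cost is one field on the event log, one rule for the comparison, and one short table. The downside is slightly fewer events in the formal comparison.

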### Statistical analysis

In accordance with Consolidated Standards of Reporting Trials (CONSORT) [94] principles, we will report all participant flow in the study. Descriptive statistics will be used to summarise assessments of feasibility and acceptability in terms of recruitment, dropout and completeness of therapy. The main efficacy analysis will be via intention-to-treat with data from all participants included in the analysis including those who do not complete therapy. When completion of the full battery of outcome measures is not possible, participants will be offered the opportunity to complete the primary outcome measure only, and as many of the main secondary outcome measures as are tolerated, in person, by telephone, or by email. Every effort will be made to follow up all participants in both arms for research assessments, and the analysis will use, where appropriate, statistical techniques for handling missing data, determined by the extent and distribution of missing data, and any identified demographic or baseline clinical predictors of missing data (age, gender, ethnicity, SDQ-E, UED severity, Severe/Other Mental Illness, borough). The primary hypothesis will be analysed using a linear mixed model allowing for the baseline measurement of SDQ-E and treatment assignment as fixed effects, with SDQ-E at 4 months as the dependent variable. Therapist effects will be modelled by including a random effect for each therapist in the therapy arm, with the control-arm participants considered as being in individual clusters of size 1. The use of a mixed (random)-effect models will allow for estimation of the intra-cluster correlation coefficient, a measure of the proportion of variance in outcome because of therapist effects, which can be used in future applications; no estimate of this is currently available. Secondary outcome measures (excluding economic outcomes) will be analysed using the same approach.

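### The primary model omits the severity stratum and borough used to stratify randomisation; to the extent that they predict outcome beyond baseline SDQ-E, standard errors are too wide and some power is lost

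*Protocol article*

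**What the plan says.** The Randomisation section uses "random permuted blocks of random size" and stratifies by a "Severe Mental Illness (i.e. psychotic illness)/Other Mental Illness factor, since this is an important prognostic factor". It adds a second factor: "We will also stratify by borough for logistical reasons, so that treatment cases are equitably allocated across therapists". The abstract's Methods paragraph names the same two factors.

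The Statistical analysis section gives the primary model for SDQ-E at 4 months as a linear mixed model "allowing for the baseline measurement of SDQ-E and treatment assignment as fixed effects", with therapist effects handled by "including a random effect for each therapist in the therapy arm, with the control-arm participants considered as being in individual clusters of size 1". Secondary outcomes other than the economic ones follow the same approach. In that section severity and borough appear only in a list of possible predictors of missing data.

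The Severe stratum is described in two ways. The abstract has "an identified psychotic or bipolar disorder"; the Randomisation section equates it with psychotic illness alone.

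**The concern.** Stratified allocation makes the arms more alike on the stratification factors than simple randomisation would. If those factors predict outcome, the treatment estimate varies less from trial to trial. A model without them does not register that gain: it leaves their variation in the residual and reports a standard error suited to simple randomisation. Confidence intervals are then wider than they need be, and the test rejects a true null less often than 5% of the time.

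The protocol supplies the premise for severity by calling it prognostic. Its Sample size section also counts on covariate adjustment to offset the precision lost to variation between therapists. Leaving out a covariate that the trial already holds works against that argument.

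For borough the case is different, since no prognostic role is claimed. Borough governs how cases are spread over therapists. Where therapists work within one borough, a model without borough can count borough differences as therapist variance, and so in the intra-cluster correlation that the trial wants to report for later use.

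**Working it through.** **Inputs from the protocol article.** 120 randomised, 60 per arm; 45 per arm followed up; effect 0.6 SD; two-sided 0.05; 2 severity levels and 4 boroughs.

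**Assumption.** R² is the share of outcome variance, after baseline SDQ-E, that the strata explain. The document gives no value, so a range of 0 to 20% is shown.

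**The plan's own figures.** A two-group t test with 45 per arm has 80.4% power at 0.6 SD and 90.7% at 0.7 SD. The stated 80% and 90% reproduce.

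**Analytic check, perfect balance.** Let k = √(1 − R²).

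- Standard error without the strata, relative to the correct one: 1/k.
- True size of the nominal 5% test: 2(1 − Φ(1.96/k)). At R² = 10%, 1.96/0.949 = 2.066, giving 3.9%. At 20%, 1.96/0.894 = 2.191, giving 2.8%.
- Power, with 0.6 taken on the residual SD scale: SE = √(2/45) = 0.211; noncentrality = 0.6/(0.211k), which is 2.846, 3.000 and 3.182 at R² = 0, 10% and 20%. On 88 degrees of freedom the critical value is 1.987. With the strata in the model the threshold is 1.987; without them it is 1.987/k (2.095 at 10%, 2.222 at 20%). Both powers come from the noncentral t distribution.

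| R² | SE too wide by | True size | Power, strata omitted | Power, strata included |
|---|---|---|---|---|
| 0 | 0% | 5.0% | 80.4% | 80.4% |
| 5% | 2.6% | 4.4% | 81.0% | 82.3% |
| 10% | 5.4% | 3.9% | 81.6% | 84.3% |
| 20% | 11.8% | 2.8% | 83.0% | 88.2% |

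Using 84 degrees of freedom for the larger model changes its power by less than 0.1 point.

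**Simulation with imperfect balance.** 120 participants were allocated in blocks of 2 or 4 within the 2 × 4 strata, and each was followed up with probability 75%; 4,000 runs per setting. Further assumptions: a quarter of participants in the Severe stratum, four-fifths of R² from severity and the rest from borough, baseline correlation 0.5, no therapist effect.

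| R² | Type I error, omitted | Type I error, included | Power, omitted | Power, included |
|---|---|---|---|---|
| 0 | 5.2% | 5.1% | 89.8% | 89.2% |
| 10% | 4.3% | 4.9% | 90.8% | 92.2% |
| 20% | 3.4% | 4.6% | 91.1% | 94.8% |

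Without the strata, the average model standard error was 0.184. The empirical value was about 0.175 at R² = 10% and 0.171 at 20%, so the excess was about 5% and 8%. Power is higher than in the analytic table because 0.6 is here on the total SD scale: with a baseline correlation of 0.5 it becomes 0.6/√0.75 = 0.69 residual SD. The Monte Carlo standard error of a 5% rate is √(0.05 × 0.95/4000) = 0.3 points.

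**The case against.** **The size is assumed.** This stands. Nothing in the document says how much the strata add once baseline SDQ-E is in the model. If they add nothing, the standard errors are right as planned. At R² = 2% they are only 1% too wide and the test runs at 4.8%. A reader might infer that all the trial's intervals and p-values are conservative; that holds only for outcomes that the strata predict.

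**Balance is imperfect among those analysed.** This also stands. Small strata, random block sizes and dropout weaken the balance, and the simulation shows smaller distortions than the formula.

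**Borough has little support as a covariate.** Partly stands. It is a stratification factor for logistical reasons only, yet takes three of the four added degrees of freedom. The Recruitment section starts in one borough and extends to others as needed, so four well-filled levels are not assured. The case for borough is analysis as randomised and a cleaner therapist variance.

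**The stated covariate list may be condensed.** The Sample size section speaks of baseline covariates in the plural. It names only distress, however, and the Statistical analysis section spells out the fixed effects, so this does not put the strata into the model.

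**Missing data.** A reader might infer that leaving out the strata undermines a missing-at-random assumption, since both are listed as possible predictors of missingness. The document does not support that: the same sentence lets identified predictors determine how missing data are handled, so both factors already have a route into the analysis.

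**Conclusion.** The omission is real, and it concerns efficiency. Randomisation is stratified on two factors, one of them called prognostic, and the stated primary model uses neither. To the extent that they predict outcome beyond baseline SDQ-E, intervals are too wide and power is lost. Over an assumed R² of 0 to 20% the excess in the standard error is 0 to 12% under perfect balance, and about 5% at R² = 10% and 8% at 20% with dropout. The power forgone is 0 to about 5 points analytically, and 1.4 points (R² = 10%) or 3.7 points (20%) in the simulation.

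A reader might go on to infer a biased treatment effect or excess false positives. Neither follows: the error is in the conservative direction and the estimate is not biased by the omission. These figures are for a continuous outcome in a linear model and leave out therapist effects.

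The two descriptions of the Severe stratum are a separate wording conflict. It matters here because a participant with bipolar disorder without psychosis would be classed differently under each.

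**What to change.** Add the severity stratum (1 degree of freedom) and borough (up to 3) as fixed effects in the primary model and in the secondary models that copy it. Use the values entered at randomisation, and state in advance how boroughs with few participants will be pooled. Severity is the main case; borough is included because allocation was stratified on it and to help keep borough differences out of the therapist variance and the intra-cluster correlation.

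Reconcile the two descriptions of the Severe stratum with the definition programmed in the randomisation system, and align the plural covariates in the Sample size section with the model actually specified.

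The cost is a sentence or two and at most four degrees of freedom out of about 90 analysed participants. No new data are needed. If the strata prove uninformative, the simulated loss is 0.6 points of power (89.8% to 89.2%). The change should be fixed before allocation is joined to the outcome data.
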